Antidepressant treatments ^d^	X			X	X
Adverse events monitoring	X	X	X	X	X
Study completion/termination record ^e^			At study exit		

^a^ QIDS-SR, Q-LES-Q-SF, EQ-5D-5L, THINC-it, GAD-7, and Health Care Utilization Form are not collected at 3, 9, and 15 months

^b^The ASRM, THINC-it, and GAD-7 are optional assessments to be completed at selected sites only and will be upto the investigators’ clinical judgment to decide which participants complete the assessments

^c^Health care utilization data (eg, number of depression-related emergency room visits and/or hospitalizations) will be obtained where possible (patient reported and/or based on medical records, whichever is available). More detailed information may be derived from a national health care database, if available, and if the patient provides consent to collect this data

^d^ Antidepressant medications and psychotropics, ECT, rTMS, and/or psychotherapy (such as interpersonal therapy and cognitive behavioural therapy)

^e^ Including participant satisfaction record (if applicable)

All participants will exit the study after completing 60 months of post-implantation follow-up, or at study end (whichever comes first). The study may be stopped when the last participant has reached the 36 months of follow-up. Study end will be communicated to all participating sites. The study will be considered completed when all enrolled participants complete the study completion/termination record.

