### Intervention (VNS therapy implant procedure and programming)

Per standard of care, all participants will be implanted with a commercially available implantable VNS Therapy System (manufactured by LivaNova) with generator, lead, and external programming system. The VNS Therapy Physician’s Manual and the Implant Manual contain instructions regarding the implantation procedure and initial device parameters/diagnostics. Surgeons performing the implantation procedures should have the appropriate qualifications and training to perform the surgery. VNS Therapy consists of a pulse generator which is surgically implanted subcutaneously in the thoracic area (usually the left side) and delivers intermittent electrical signals to the vagus nerve via a lead that is partially wrapped around the vagus nerve in the mid-cervical region. The electrical signals are relayed to various regions of the brain. The system is programmed via an external programming device (see Fig. 1).

Following device implantation, the device must be switched ON and titrated to clinical efficacy as per standard medical care. Clinicians program the system using an external programming device and rely on attentive patient-specific titration to select the right combination of adjustable parameters (output current, frequency, pulse width, and signal ON and OFF times) to attain full activation of the vagus nerve while minimizing stimulation-induced side effects. Usually stimulation is delivered intermittently, typically 30 s ON, 5 min OFF. The rate of titration varies by patient and their response until a therapeutic dose has been established; all sites are encouraged to reach a stimulation of minimally 1 mA (considered minimal therapeutic dose) at a duty cycle of minimally 10%. This recommendation is based on previous findings that a higher delivered charge predicted greater sustained antidepressant effects [38].

The sponsor has developed detailed metrics on the titration procedure to assist clinicians reach the optimal therapeutic dose of VNS for individual patients. Patients who are under-dosed and do not achieve the therapeutic dose of VNS will be identified via a so-called ‘risk-based study monitoring’ method. The sponsor will contact sites that have patients below therapeutic dose and if needed the sponsor will provide technical support to the principal investigators on titrating VNS parameters to reach the minimal therapeutic dose as reasonably possible.

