### Safety assessments

All participants will be monitored for safety and evaluated for any depressive symptoms (including suicidal ideation) by completing study assessments throughout the study. Additionally, the participants will be instructed to contact their physician in case of worsening depression/suicidality. The sponsor is responsible for the ongoing safety evaluation of the VNS Therapy system, review of reported adverse events, investigation of unanticipated serious adverse device effects, and notification of regulatory authorities per applicable requirements.

For safety evaluation, data will be collected on adverse events, serious adverse events, VNS Therapy related adverse events and serious adverse events (including the use of the device), unanticipated adverse device effects, and device deficiencies. Adverse events will be followed until (a) resolution, (b) stabilization, (c) the end of the study, or (d) if a study physician and/or sponsor determines that a device-related adverse event must be followed until its conclusion which extends beyond the end of the study.

The study physicians should reference the VNS Therapy Physician’s Manual for a list of anticipated adverse events that have been frequently reported in clinical studies. Any serious adverse device effect not listed in the Physician’s Manual will be considered as unanticipated.

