### Sample size and statistical analysis considerations

As this is an observational study designed to describe the characteristics of VNS Therapy in a real-world setting, the statistical analysis of the study outcomes will focus on a combination of descriptive and exploratory statistics, rather than confirmation of formal hypothesis testing; that is, the provision of two-sided 95% confidence intervals rather than *p*-values. As an additional consequence, the emphasis provided in the study will be on the precision of the estimate. A sample size of 500 patients is sufficient to provide higher precision of the estimates in term of width of the 95% confidence interval for the key study endpoints:
For the primary endpoint based on MADRS, the width of the 95% CI will be of 7.8% assuming an observed response of approximately 25%.For the secondary endpoint based on Q-LES-Q-SF response (and the available Q-LES-Q-SF data obtained in the D-23 study), the width of the 95% CI will be 8.9% assuming an observed response of approximately 50% [49].

Enrolled analysis population will include all participants who signed the informed consent and who satisfy the study eligibility criteria. Safety analysis population will include all enrolled participants who were implanted with the VNS Therapy system and received at least one dose of stimulation. The full analysis set population will include all participants in the safety analysis population with evaluable baseline device data; that is, patients who have the device implanted and received at least one dose of stimulation. As such, for this study, the full analysis set population is equivalent to the safety analysis population.

The full analysis set population will be used mainly for all effectiveness and efficiency summaries and is considered the primary population. Descriptive statistics will be calculated using as reference the number of participants in the relevant analysis population, according to the nature of the data (i.e., continuous, discrete, time to event) as follows: continuous variables by number of non-missing observations, arithmetic mean, standard deviation, minimum and maximum values, median and quartiles and categorical variables by absolute and relative frequencies.

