#### Safety analysis

Safety data will be summarized descriptively, based on the safety analysis population (defined above). Adverse event data will be summarized by means of number of participants with at least one event, incidence rates, crude incidence rates. Similarly, statistics for serious adverse event; adverse device effect; serious adverse device effect; unanticipated serious adverse device effect and deaths will be presented.

Note that an adverse event with a ‘related’ causal relationship to the VNS therapy will be considered an Adverse Device Effect. Details of any recorded device deficiencies will be listed. Further safety tabulations may be presented, as appropriate.

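### The safety population requires at least one dose of stimulation, so implanted participants who are never stimulated drop out of the adverse event and death summaries, and peri-implant rates can be understated

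*Protocol article*

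**What the plan says.** The section Sample size and statistical analysis considerations defines the set: "Safety analysis population will include all enrolled participants who were implanted with the VNS Therapy system and received at least one dose of stimulation". It then states that the full analysis set is the same group, and takes the size of the relevant analysis population as the reference for descriptive statistics. No set of all implanted participants is defined.

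The Safety analysis section ties its output to that set: "Safety data will be summarized descriptively, based on the safety analysis population (defined above"). The output covers adverse events, serious adverse events, adverse device effects (including serious and unanticipated serious ones) and deaths. Two further sentences there matter: "Details of any recorded device deficiencies will be listed", and "Further safety tabulations may be presented, as appropriate".

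Collection is wider than analysis. The Safety assessments section says "All participants will be monitored for safety", and the data to be collected include "unanticipated adverse device effects, and device deficiencies". Table 1 marks adverse events in all five visit columns ("Adverse events monitoring X X X X X"), the second of which is implant, Day 0. It also schedules device deficiency monitoring from the implant visit.

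The Intervention section makes activation a step after surgery: "Following device implantation, the device must be switched ON and titrated to clinical efficacy as per standard medical care".

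**The concern.** For an implanted device, exposure to harm begins with the operation. The stimulation condition makes membership of the safety set depend on something that happens afterwards. Infection, nerve or wound injury, a lead or generator fault, early explant or death can each be the reason why stimulation never starts. The participants removed are then selected partly by the outcome being counted.

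At stake is the peri-implant event rate. The Discussion expects the results to inform the use of the therapy as effective and safe and perhaps to widen access to it. Serious peri-implant events are likely to be few, so the loss of a handful of cases could move their rate noticeably.

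**Working it through.** **Reading the rules together**

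1. Entry to the safety set: enrolled, implanted and stimulated at least once (Sample size and statistical analysis considerations).
2. Summaries based on that set: adverse events, serious adverse events, device effects and deaths (Safety analysis).
3. Start of collection: adverse events from baseline, device deficiencies from Day 0 (Table 1).
4. Order of steps: surgery first, activation afterwards (Intervention).

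An implanted participant who is never stimulated fails condition 1. Under rule 2, that person's events are absent from the numerator and the person is absent from the denominator, although rule 3 means the events were recorded. The full analysis set does not recover them, because it is declared equivalent.

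**Size**

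The article gives neither a number of never-stimulated participants nor a complication rate, so there is no stated figure on this point to reproduce. The planned 500 implants come from the article. Everything else below is assumed.

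*Illustration A: fixed rate among stimulated participants.* Let m be the number never stimulated, q their event rate, and 3% the event rate among stimulated participants.

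- Expected events in the planned safety set: 0.03 × (500 − m); the reported rate is always 3.0%.
- Rate in all implanted participants: [0.03 × (500 − m) + q × m] / 500.
- Share of events missed: q × m / [0.03 × (500 − m) + q × m].

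| m | q | Expected events, all implanted | Rate, all implanted | Share missed |
|---|---|---|---|---|
| 0 | – | 15.00 | 3.0% | 0% |
| 1 | 50% | 14.97 + 0.5 = 15.47 | 3.1% | 3% |
| 1 | 100% | 14.97 + 1 = 15.97 | 3.2% | 6% |
| 5 | 50% | 14.85 + 2.5 = 17.35 | 3.5% | 14% |
| 5 | 100% | 14.85 + 5 = 19.85 | 4.0% | 25% |
| 10 | 50% | 14.70 + 5 = 19.70 | 3.9% | 25% |
| 10 | 100% | 14.70 + 10 = 24.70 | 4.9% | 40% (0.405) |
| 15 | 50% | 14.55 + 7.5 = 22.05 | 4.4% | 34% |
| 15 | 100% | 14.55 + 15 = 29.55 | 5.9% | 51% |

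*Illustration B: fixed total.* Take 15 events in 500 implants, a rate of 3.0%.

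- 5 never stimulated, 3 of them with an event: (15 − 3)/(500 − 5) = 12/495 = 2.42%; 3/15 = 20% of events missed.
- 10 never stimulated, 6 with an event: 9/490 = 1.84%; 6/15 = 40% missed.
- 25 never stimulated, 8 with an event: 7/475 = 1.47%; 8/15 = 53% missed.

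**Direction**

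The rate is understated when events are more frequent among never-stimulated participants than among stimulated ones (q above 3% in illustration A). If all of them simply withdrew without an event (q = 0), the error reverses: with m = 15, the all-implanted rate is 14.55/500 = 2.91% against 3.0% reported. The reversal is slight, whereas the understatement can be large.

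**The case against.** The strongest case on the other side has four parts.

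- **Few participants are affected.** The Intervention section requires activation after implantation, so never-stimulated cases should be exceptions. The article also does not say when the first dose is delivered, or whether anything done with the device on Day 0 counts as one. This stands as a limit on size. It does not rescue the rule: the requirement is an instruction that a complication can defeat, and if nobody were excluded the condition would do nothing.
- **Device failures are still reported.** A reader might infer that a fault which prevented stimulation disappears from all safety output. The article does not support that: "Details of any recorded device deficiencies will be listed" is naturally read as covering every deficiency logged from Day 0. The section's opening sentence could be taken to limit the listing too, so the matter is at worst ambiguous. A listing nevertheless has no denominator, and it does not cover surgical adverse events or deaths.
- **Other routes exist.** Disposition will show numbers implanted and reasons for discontinuation. Sponsor review and regulatory notification continue for everyone, and further tabulations are possible. No data are lost at collection. None of these routes gives an adverse event rate that includes the never-stimulated, and the further tabulations are optional with no population named.
- **The study is descriptive.** There is no safety hypothesis or threshold, and the primary endpoint is response at 12 months. This stands, and it lowers the priority of the point.

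**Conclusion.** The point holds as a badly fixed analysis population. Followed as written, the rule removes never-stimulated implanted participants from the adverse event, device-effect and death summaries through an event that the harm can itself cause. It is an express definition, so it is not detail that an article leaves to a fuller document.

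Three stronger readings are not supported. Surgical complications as a class are not excluded: those in participants who are later stimulated, even once, remain counted. Device deficiencies cannot be said to go unreported, given the separate listing. And a reader might infer a definite understatement of 20% to 50%, but such a figure comes only from the chosen assumptions. With 500 implants and about a 3% event rate, the share of events missed starts at zero, is 3% to 6% with one never-stimulated participant, and reaches about 50% only with 15 to 25 such participants who have high event rates. The true number is unknown and probably towards the low end.

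This should be fixed, but it is not a defect on which the study's primary result depends.

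**What to change.** - Define the safety population as all enrolled participants in whom VNS implantation was performed or attempted, whether or not stimulation was ever delivered. Count events from the start of surgery.
- Keep the stimulated subset for the effectiveness analyses, and for stimulation-related safety summaries presented in addition.
- Delete the statement that the full analysis set and the safety population are equivalent.

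The cost is a change to one definition and the removal of one sentence, carried into the analysis plan. No new data are needed, because Table 1 already collects adverse events from baseline and device deficiencies from the implant visit. The downside is that reported surgical event rates may become slightly less favourable.

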#### Study participants

Participant disposition including the number of participants enrolled/implanted and the numbers completing or discontinuing (including the reason for discontinuation) will be provided. Information on demographics, implant characteristics, medical history, medications, and treatments will be summarized as appropriate.

#### Primary analysis

The primary endpoint of response ─ defined as a decrease in MADRS total score of at least 50% from baseline to 12 months post-implant ─ will be provided for patients who were experiencing a major depressive episode at the time of enrolment (i.e. a baseline MADRS total score ≥ 20). The number and percentage of participants with response and the associated 95% confidence interval will be presented.

#### Secondary efficacy analyses

The secondary analyses will include response duration and changes in mood, severity of depression, mania, quality of life, psychosocial impairment, cognition, anxiety, suicidality, and adjunctive antidepressant treatment usage. Absolute scores and changes from baseline in each of the continuous secondary endpoints will be summarized for each of the follow-up assessments; and 95% confidence intervals for the changes will be presented.

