**Secondary outcome measures**	
Duration of response	The difference between the first recorded date of post-baseline MADRS score when response is achieved (based on a decrease in baseline MADRS score of ≥50%) and the first date at which the MADRS score reaches a level of < 40% from baseline.
Duration of response	Change in MADRS score over time
Duration of response	Cumulative percentage of first-time responders (based on reduction in baseline MADRS score of ≥50%) and cumulative remission (based on MADRS score of ≤9 at any post-baseline visit) over time.
Changes in mood, depression, and mania scores	This will be based on changes in MADRS, QIDS-SR, and ASRM. The QIDS-SR questionnaire measures symptoms of mood and depression [41]. The ASRM measures the presence and severity of manic and hypomanic symptoms, specifically in patients diagnosed with bipolar disorder [42]. Note: ASRM is an optional assessment.
Changes in quality of life and psychosocial impairment	The WPAI:D questionnaire measures impairments in work and activities in depression [43]. The Q-LES-Q-SF scale measures the degree of enjoyment and satisfaction experienced during the past week [44]. The EQ-5D-5L questionnaire measures generic health status and quality of life [45].
Changes in suicidality	Based on Item Number 10 of MADRS and Item Number 12 of QIDS-SR.
Changes in antidepressant treatments	This will include data on drug dosage and type of antidepressant medications, and duration and intervals of maintenance ECT, rTMS, and/or psychotherapy.
Changes in cognition	THINC-it® Tool includes the 5-item PDQ-5, in addition to 4 traditional cognitive assessments which have been reconfigured for computer-based administration. Thus, it assesses both a patient’s subjective assessment as well as key objective measures of cognitive function [46]. Note: THINC-it is an optional assessment.
Changes in anxiety	The GAD-7 measures severity of generalized anxiety disorder [47]. Note: GAD-7 is an optional assessment.

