As the study will assess VNS Therapy for the treatment of patients in a real-world setting, it may potentially have several related limitations, including the lack of randomization and blinding of participants and clinicians, the lack of a control group, potential attrition of participants and deviations in the delivery of the intervention, differential optimization of VNS parameter settings, differential use of concomitant anti-depressant medications and treatments in patients, and the heterogeneous study population may limit generalizability. The suicidality assessment may be limited as it will be assessed based on a single item in the MADRS scale and a single item in the QIDS-SR scale, instead of being assessed using a specific suicidality scale. In addition, this will be a 5-year longitudinal study and participant attrition over time may decrease the sample sizes at each analysis time point.

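### Visit-by-visit observed means for the continuous secondary endpoints can show sustained or growing improvement with no true change if participants who do poorly leave

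*Protocol article*

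**What the plan says.** The protocol article, under Secondary efficacy analyses, states that absolute scores and "changes from baseline in each of the continuous secondary endpoints will be summarized for each of the follow-up assessments", and that intervals for the changes will be given. Under Sample size and statistical analysis considerations it describes "continuous variables by number of non-missing observations, arithmetic mean, standard deviation" and further descriptive statistics, mainly in the full analysis set. Inference is by "the provision of two-sided 95% confidence intervals rather than" p-values.

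Study aims asks whether benefit is achieved and maintained over the short, middle and long term. Study design sets follow-up at 36 to 60 months. The notes to Table 1 allow the study to close once the final enrollee has three years of follow-up.

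The Discussion lists possible attrition and the absence of a control among the limitations, then adds that "participant attrition over time may decrease the sample sizes at each analysis time point". It names no other consequence of attrition. The subsection Study participants promises discontinuations with their reasons.

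Table 2 defines change in suicidality as "Based on Item Number 10 of MADRS and Item Number 12 of QIDS-SR". Deaths and serious adverse events are tabulated separately under Safety analysis.

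**The concern.** A mean over whoever attends a visit estimates the mean for all implanted participants only if attendance is unrelated to outcome. Over three to five years in difficult-to-treat depression, that is a strong assumption. If people with poor scores are more likely to leave, each later mean comes from a better-selected group. The curve then holds or improves even when no individual changes, which is the pattern the study hopes to see. With no control group, there is no comparison that would show it.

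The stated consequence of attrition, smaller samples, is the less serious one. Smaller samples widen the interval, and the reader can see that. Selection moves the centre of the interval, and nothing in the interval shows it.

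Suicidality is the sharpest case. A participant who dies by suicide has no later item score, so the item mean loses the worst outcome.

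**Working it through.** **The plan's own figures.** The article says "A sample size of 500 patients is sufficient to provide higher precision of the estimates" and gives 95% interval widths of 7.8% at 25% response and 8.9% at 50%. Exact (Clopper-Pearson) intervals reproduce both: 125/500 gives 7.77% and 250/500 gives 8.94%. Both use all 500 and make no allowance for loss. The article gives no precision figure for mean changes, no drop-out rate and no standard deviation.

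**Size of the shift.** Let *d* be the fraction missing at a visit and *g* how many points less the missing participants improved than those observed. The full-population mean is (1 − *d*) × (observed mean) + *d* × (missing mean). The observed mean therefore overstates improvement by *d* × *g*.

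The 95% half-width is 1.96 × SD / √(500 × (1 − *d*)). SD = 10 MADRS points is an assumption, as are all values of *d* and *g*.

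| Missing *d* | Half-width | Shift, *g* = 0 | Shift, *g* = 5 | Shift, *g* = 10 | *g* at which shift equals half-width |
|---|---|---|---|---|---|
| 10% | 0.92 | 0 | 0.5 | 1.0 | 9.2 |
| 20% | 0.98 | 0 | 1.0 | 2.0 | 4.9 |
| 30% | 1.05 | 0 | 1.5 | 3.0 | 3.5 |
| 40% | 1.13 | 0 | 2.0 | 4.0 | 2.8 |

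A negative *g* (good responders leaving) gives the same sizes with the opposite sign.

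**The two effects of attrition compared.** With all 500 observed, the half-width is 1.96 × 10 / √500 = 0.88. At 40% missing it is 1.13, so lost sample size costs 0.25 points. Selection with *g* = 5 costs 2.0.

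**Drift over time.** A simulation used a flat true mean change of −10, between-patient SD 7 and within-patient SD 6 (all assumed), with drop-out after each scheduled visit depending on the score at that visit.

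| Drop-out | Observed mean, month 12 | Month 36 | Month 60 | Retained at 60 |
|---|---|---|---|---|
| Unrelated to score | −10.0 | −10.0 | −10.0 | 67% |
| Moderately higher with poor score | −10.3 | −10.7 | −11.0 | 65% |
| More strongly higher with poor score | −10.7 | −11.5 | −12.2 | 60% |

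The last two rows would read as slowly growing benefit, yet no true change occurs after month 12.

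**Does the remedy work?** A separate simulation assumed true changes of −8 at month 12 and −10 at month 36, SD 10, within-person correlation 0.7 and 25–40% drop-out by month 36 depending on the last score (log-odds 0.7–1.1 per SD). Observed means at month 36 were −11.3 to −13.0. A likelihood-based estimate returned about −8.0 and −10.0. Because drop-out depended only on observed scores, that recovery follows from the set-up. It shows what the model does under missing-at-random, not that missing-at-random holds here.

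**The case against.** The strongest reply is that this is a condensed article. Missing-data rules and model details usually sit in the statistical analysis plan, which is not shown, so their absence is no finding. That is right, and no absence is claimed. The point concerns the method the article does name, set against the aim it serves.

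Several stronger readings are tempting and are not supported:

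- *That only non-missing data will ever be analysed.* A count of non-missing values is one listed statistic. The article announces descriptive and exploratory analyses and excludes no model.
- *That improvement will look larger.* No figure shows who leaves. Concomitant treatments allows any added depression treatment, so a non-responder need not leave in order to change therapy.
- *That explanted participants are lost.* Table 1 lists explant as an as-needed procedure and does not say that it ends participation.
- *That attrition is regarded purely as lost numbers.* The Discussion also lists it as a general limitation. It just never names selection.
- *That all durability conclusions depend on these means.* Table 2 also has a date-based duration of response and cumulative first response and remission. The quoted sentence covers continuous endpoints only.
- *That suicide deaths disappear.* They are reported under Safety analysis. Scoring them as a worst category would be a choice of estimand, not the correction of an error.

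It is also fair that, in a descriptive study, observed-case tables are a natural display. They should stay. They are a weak sole basis for a statement that benefit is sustained.

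**Conclusion.** The point holds as a weakness in the stated method, not as a demonstrated bias. The continuous secondary summaries, as described, are open to selection by outcome-related attrition over 36 to 60 months, with no control group to reveal it.

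With 20–40% missing and leavers improving 5 MADRS points less, the shift is 1–2 points, equal to or larger than a half-width of about 1 point. At 10% missing and the same gap it is 0.5, inside the interval. With no gap it is zero. Every one of these sizes rests on assumed drop-out, SD and gap, because the article supplies none. Some loss between months 36 and 60 will be administrative, set by enrolment date rather than response, and should not be counted as drop-out.

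**What to change.** 1. For each continuous secondary endpoint, estimate change from baseline at each visit from a mixed model for repeated measures, with categorical visit, baseline score and unstructured covariance, using all scheduled visits. Keep the observed-case tables as support.
2. Compare baseline and last observed scores of leavers and stayers, and separate administrative end of follow-up after month 36 from drop-out.
3. In the Discussion, name selection bias as well as smaller samples as a consequence of attrition.
4. Present suicide deaths and attempts, which fall within the adverse-event collection, beside the item-score suicidality summary. The model does not itself handle death: under missing-at-random it implicitly projects scores for people who have died.

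If the analysis plan already contains such a model, one sentence in the protocol saying so would cover item 1.

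The cost is some wording and modest programming, with no new data: MADRS is scheduled at nine follow-up visits to month 36, and discontinuation reasons are already to be reported. The model relies on missing-at-random, which cannot be verified but is weaker than what observed-case means assume.
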